#### Data analysis

As this trial follows a randomised, parallel group, non-inferiority design, data will be analysed and reported according to both Consolidated Standards Of Reporting Trials (CONSORT) guidelines^50^ and the non-inferiority trials CONSORT extension.^51^ Baseline data, including demographic characteristics (eg, age, gender) and clinical measures (eg, BAT, RCADS), will be reported between the two randomised groups. Jones *et al*
49 recommend both per-protocol and intention-to-treat (ITT) analyses for non-inferiority designs. For an equivalence or non-inferiority trial, as opposed to a comparative trial, ITT analyses are not considered conservative, as any blurring of the difference between the treatment groups increases the chance of declaring equivalence. We follow this recommendation with the refinement that the main analysis of the primary outcome will be per protocol (or completers only) with a sensitivity analysis on the ITT population.^49^ We will require both the per-protocol and ITT analyses to demonstrate conclusive evidence to declare that OST is ‘non-inferior’ to multisession CBT. If the results of the analysis are discrepant (eg, the ITT rejects the null of inferiority but the per-protocol analysis does not or vice versa) then we will report the conflicting results from both analyses highlighting the inconclusive nature of the results. For the sake of the analysis, a participant in the OST group is defined as per protocol if they attend both the initial functional assessment and the rapid exposure therapy session. A participant in the CBT group is defined as per protocol if they attend at least four CBT sessions.

The primary outcome (mean BAT score at 6 months) and the secondary outcomes (ADIS, CAIS, EQ-5D-Y, CHU-9D, RCADS and goal-based outcome scores) will be compared between groups using mixed-effects linear regression with exchangeable correlation to allow for the clustering of outcomes within therapist. The analysis will be conducted controlling for baseline BAT score, site and stratifying variables (age group and baseline phobia severity). The null hypothesis of inferiority will be rejected if the two-sided 95% CI for the difference is wholly below 0.4 (the range of clinical non-inferiority).

We anticipate some drop-out/attrition, so case missing data may be an issue. Case and item missing data will be examined and multiple imputation methods will be used to reduce bias due to any missing responses in both the per-protocol and the ITT analyses. Where appropriate, modelling methods that generate robust SEs in the presence of missing data will be considered.

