#### Behavioural avoidance task

The primary outcome is the behavioural avoidance task (BAT) at 6 months postrandomisation. The BAT is a widely used measure of treatment outcomes for phobias in children.^6 21^ The BATs for the Alleviating Specific Phobias Experienced by Children Trial (ASPECT) trial are standardised for each stimulus and have been found to have good test–retest reliability^20 29^ and strong correlation with other outcome measures of anxiety and phobia.^30 31^ During a BAT, the child gradually confronts their phobic stimulus over 10 predefined steps of increasing difficulty; the child does not have to complete all the steps. For example, a child with spider phobia may start the BAT at step 0, standing outside of a room that has a spider contained in a box. Subsequent steps the child may take are: opening the door (step 1), passing through the doorway (step 2), through to holding the spider for 20 s (step 10). The number of steps the participant takes is the main unit of measurement recorded for analysis. The BAT also includes a measure of subjective units of distress whereby the child reports their level of fear at the start of the BAT, and at the last step completed (ranging from 0=no fear at all to 8=extreme fear).

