#### Resource Utilisation Questionnaire

We developed a bespoke questionnaire to assess use of healthcare and other resources, based on a previous Resource Utilisation Questionnaire by Barrett and colleagues^45^ and its adaptations for younger populations by members of our research team^45–47^ The questionnaire is completed by the parent and collects data on resource and service utilisation relating to the child over the previous 6 months on: general health and community service use (ie, appointments with GP’s, nurses, social services and educational services); mental health service use (ie, appointments with a psychiatrist, psychotherapists, psychologists, CAMHS therapists and other forms of mental health support); hospital-based services (ie, visits to A&E, urgent care centres and hospital stays); days missed from school by the child; days missed by parents/carers from work or studies.

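### Per-protocol status rests on attendance at allocated sessions alone, so children who also receive other phobia therapy before the 6-month BAT stay in the main analysis

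*Protocol article*

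**What the plan says.** All the rules at issue are in the Data analysis section of the protocol article.

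- OST arm: a child is "defined as per protocol if they attend both the initial functional assessment and the rapid exposure therapy session".
- CBT arm: "A participant in the CBT group is defined as per protocol if they attend at least four CBT sessions".
- Role of the two sets: "the main analysis of the primary outcome will be per protocol (or completers only) with a sensitivity analysis on the ITT population".
- Decision rule: "We will require both the per-protocol and ITT analyses to demonstrate conclusive evidence to declare that OST is ‘non-inferior’ to multisession CBT".
- Reason for not relying on ITT: "any blurring of the difference between the treatment groups increases the chance of declaring equivalence".

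On timing, the section on the behavioural avoidance task says: "The primary outcome is the behavioural avoidance task (BAT) at 6 months postrandomisation". The Interventions section describes OST as a 1-hour planning session and one treatment session of about 3 hours, followed by practice at home. It gives a range of 4 to 20 sessions for CBT, usually weekly or fortnightly.

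On information about other therapy, the Resource Utilisation Questionnaire asks parents about "mental health service use (ie, appointments with a psychiatrist, psychotherapists, psychologists, CAMHS therapists and other forms of mental health support" over the previous 6 months. The Economic evaluation section uses these data for costs. Contamination is mentioned once, under Public and patient involvement, as a topic that was discussed; no analysis rule is attached to it.

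**The concern.** A per-protocol analysis guards against blurring only if its definition removes, or otherwise deals with, the children whose treatment was blurred. This definition deals with one kind, too little of the allocated treatment. It is silent on the other kind, allocated treatment plus something else. A child who attends both OST visits, remains phobic and then has a course of CBT meets the OST definition, and the BAT measured after that CBT is analysed as an OST result.

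The wording reads as a complete definition, and the article itself equates per protocol with completing treatment. This is therefore a rule fixed in the article, not a detail left open for an analysis plan.

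The non-inferiority claim is at stake. If OST were worse, the children it failed could be those most likely to get further help, and their improved scores would narrow the observed gap in both required analyses. With no midpoint outcomes (stated under strengths and limitations), no earlier BAT is available to fall back on.

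**Working it through.** **Reproducing the plan's figure.** Inputs from the Sample size section: margin 0.4 SD, baseline–final correlation 0.5, one-sided 2.5%, power 90%, 15 patients per therapist, intraclass correlation 0.01, drop-out 20%.

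- Adjusted SD = √(1 − 0.5²) = 0.866.
- n per arm = 2 × 0.75 × (1.960 + 1.282)² / 0.4² ≈ 99 (stated: 100).
- Design effect = 1 + 14 × 0.01 = 1.14; 100 × 1.14 = 114.
- 114 / 0.8 = 142.5, rounded up to 143 per arm, 286 in total, as stated.

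**Precision implied by the plan.** Effective n per arm = 114 / 1.14 = 100. SE = √(2 × 0.75 / 100) = 0.1225 SD. Power with no true difference = Φ(0.4/0.1225 − 1.96) = 90.4%.

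**Effect of added therapy.** Let a share c of the OST children and a share d of the CBT children in the analysis set receive non-allocated phobia therapy, each gaining g SD on the BAT. The observed deficit of OST then shrinks by (c − d) × g. If the true deficit equals the margin,

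P(declare non-inferiority) = Φ((c − d) × g / 0.1225 − 1.96).

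The article gives no value for c, d or g. The table assumes d = 0. A gain of 0.4 SD takes the average OST child to the CBT mean; 0.8 SD is a harsher case.

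| Share of OST children, c | g = 0.4 SD | g = 0.8 SD |
|---|---|---|
| 0% | 2.5% | 2.5% |
| 5% | 3.6% | 5.1% |
| 10% | 5.1% | 9.6% |
| 20% | 9.6% | 25.7% |

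Example: c = 10%, g = 0.4 gives a shift of 0.04 SD; 0.04/0.1225 − 1.96 = −1.633, and Φ(−1.633) = 5.1%.

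If c = d the shift is zero, and if d exceeds c it runs against OST. The table gives the error of a single analysis. The joint rule cannot raise it, but it does not remove the shift either, because the same BAT scores enter both sets.

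**The case against.** **The analysis plan may say more.** This is a condensed article, and further deviation criteria are often left to the analysis plan. That lowers certainty about what will be done. It does not repair a definition that the article states in full.

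**Switching is not shown.** A reader might infer that the trial is biased towards non-inferiority, or that later CBT is its main source of blurring. The documents support neither. The Recruitment section describes routes into the trial, not what happens to a child still phobic after OST. Non-attendance, which the definition does address, and poor fidelity also blur the arms.

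**The opportunity is not clearly one-sided.** A short CBT course can end well before 6 months. Practitioners who treat phobias at the sites are trained in OST, so CBT children could also receive something else. OST itself continues through home practice. The direction of any bias is therefore plausible but not established.

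**ITT is not at fault.** In a pragmatic trial, keeping these outcomes in the randomised arm is what ITT means. This stands: the flaw lies in the per-protocol set, which was chosen for the opposite purpose.

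**The figures are a stress case.** They put the true deficit exactly at the margin, allow no extra therapy in the CBT arm, and use the full evaluable sample. A smaller per-protocol set would have a larger SE, and hence less inflation for the same shift.

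**A strict remedy could mislead.** A reader might want non-inferiority to hold also with every switched child set to the baseline BAT. If the arms are truly equal, the gain from baseline is 0.8 SD and only OST children switch, 10% switching lowers the OST mean by 0.08 SD, and power falls to Φ(0.32/0.1225 − 1.96) = 74%. At 20% it is Φ(0.24/0.1225 − 1.96) = 50%. That is too high a price for a compulsory condition.

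**Conclusion.** The point holds as a flaw in a stated rule. Per-protocol status depends on attendance only, so the main analysis does not do what the article says it was chosen to do, and the requirement for ITT success offers no protection against this particular problem.

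Bias towards non-inferiority is a risk, not a demonstrated fact. It needs three things: non-allocated phobia therapy occurs before the BAT, it helps, and it is more common after OST than in the CBT arm. If all three hold, the effect need not be small. On the plan's own precision, 10% switching with a 0.4 SD gain roughly doubles the one-sided error and 20% nearly quadruples it. Those rates and gains are assumptions. The sample size of 286 is unaffected.

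**What to change.** 1. Leave the ITT analysis as it is.
2. Amend the per-protocol definition so that receipt, before the 6-month BAT, of the other arm's therapy or of other structured psychological therapy for the phobia is a deviation, in either arm.
3. Identify such children from therapy session records and the mental-health items of the Resource Utilisation Questionnaire. State the limits of this source: the items are recalled by parents and, as described, do not record what the therapy contained.
4. Report the number of such children by arm.
5. Do not stop at excluding them, since that could selectively remove children for whom OST failed. Pre-specify a supportive sensitivity analysis that keeps them in their arm without crediting the later BAT to the allocated treatment, for example by imputing under a range of reduced-benefit assumptions with the baseline value as the extreme case.
6. Report whether the non-inferiority conclusion survives across that range. Do not make the baseline-value analysis a third condition for declaring non-inferiority.

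The cost is a change of wording, a little extra analysis, and possibly a more cautious conclusion if switching proves common. The questionnaire items are already collected; the article does not say whether therapy records capture treatment after OST, so that should be checked. The change concerns analysis sets only and implies nothing about what further care a child should be offered.

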### Randomisation

Following written consent and completion of the baseline measures, random allocation to treatment groups is carried out remotely through a secure web-based programme designed by the Sheffield Clinical Trials Research Unit (CTRU). The randomisation allocation ratio is 1:1 to facilitate equal sample sizes across both the OST and CBT groups. Randomisation is stratified according to two age groups (7–11 years old vs 12–16 years old) and two phobia severity groups (mild to moderate vs severe); we use random permuted blocks of variable size to ensure enough participants are allocated evenly to each arm of the trial within each stratum.

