### Outcome measures

We are collecting demographic information (eg, age, gender, etc) from all children/young people and their parents. Children and parents are also asked if they have a treatment preference at baseline, although this does not affect their randomisation in any way. Participants complete the following measures at baseline and then at 6 months follow-up.

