#### Goal-based outcome measure

A goal-based outcome measure is a method of comparing how far a participant feels they have moved towards reaching a specific goal they have set before the intervention has begun. A goal-based outcome measure based on recent guidelines^44^ will be used to set up to three goals at baseline, with progress towards meeting these goals rated on a 10-point scale at the 6-month follow-up point. Progress can range from 0 (ie, goal not met), to 5 (ie, halfway to reaching the goal), through to 10 (ie, goal reached). For example, a participant with a dog phobia may set as their goal that they would like to be able to spend teatime at their grandmother’s house where there is a dog.

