### Statistical analysis

#### Sample size

The proposed sample size and non-inferiority margin are based on two separate Cochrane reviews looking at the effects of psychotherapy for those experiencing anxiety. First, Wolitzky-Taylor *et al*
47 conducted a review on studies that used both observer-rated BAT-like assessments and self-report questionnaires on adults with specific phobias and reported an overall, large effect size of d=0.81. However, as the treatment may have a different effect on children, we also examined the review of Reynolds *et al*.^48^ This review was conducted on studies of children with specific phobias but used self-report questionnaires rather than observer-rated BATs. The review reported a large effect size (d=0.85) for multisession CBT. Prior meta-analyses suggest that a standardised mean difference of around 0.8 on the BAT scale is clinically important. Therefore, we set the non-inferiority margin to be half of this at 0.4.^49^ Assuming a correlation of 0.5 between baseline and final BAT measure, we would require 200 participants (100 in each arm) to have 90% power with a 2.5% one-sided significance level to demonstrate non-inferiority of OST compared with CBT. The therapy is delivered by therapists who will see approximately 15 patients each and we anticipate a weak therapist effect (intraclass correlation coefficient=0.01). This clustering will lead to a design effect of 1.14 which increases the number required per arm to 114. We further assume a 20% drop-out rate suggesting that total number of 286 children and young people (143 per arm) will need to be recruited to the study to demonstrate non-inferiority of OST compared with CBT.

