The primary economic analysis will be cost–utility analysis conducted over the trial follow-up period (6 months). Total costs, including the intervention cost and service utilisation costs, and QALYs, will be compared between the two interventions. Unadjusted costs and outcomes will be presented in a descriptive analysis using parametric and non-parametric tests. The statistical analysis will compare mean costs and QALYs using a regression model. The regression analysis will control for baseline differences in utility.^56^ The specification of the model will follow the approach recommended by Glick *et al*
57 which considers the distribution of the dependent variable as well as any correlation between the cost and QALY outcomes. The regression coefficient on treatment will then represent the difference in mean cost and mean QALYs between groups. A bootstrap method will be used to produce CIs around the cost and QALY differences due to the likely skewness in the distribution of regression residuals.^58^ To present this in the UK decision-making context, the results will be in the conventional form of a cost-effectiveness acceptability curve (CEAC). CEAC presents the probability of the intervention being cost-effective over a range of willingness-to-pay (WTP) thresholds per QALY.^59^ The higher the probability, the more likely it is that the treatment is cost-effective at the particular WTP threshold.

The following sensitivity analyses will be conducted; (1) a cost–utility analysis using the CHU-9D instrument instead of EQ-5D; (2) a cost-effectiveness analysis using a phobia-specific measure instead of a utility-based measure and (3) cost–utility analysis from a health services perspective.

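### As written, five secondary outcomes are adjusted for baseline BAT but not for their own collected baseline, which probably costs some precision; the primary analysis and N=286 are unaffected

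*Protocol article*

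**What the plan says.** The Data analysis section names the mean BAT score at 6 months as the primary outcome and continues: "the secondary outcomes (ADIS, CAIS, EQ-5D-Y, CHU-9D, RCADS and goal-based outcome scores) will be compared between groups using mixed-effects linear regression". The next sentence gives the only covariate list: "The analysis will be conducted controlling for baseline BAT score, site and stratifying variables (age group and baseline phobia severity"). It carries no restriction to the primary outcome and names no other baseline score.

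The Outcome measures section introduces the instruments with "Participants complete the following measures at baseline and then at 6 months follow-up". Own baseline scores therefore exist for ADIS, CAIS, RCADS, EQ-5D-Y and CHU-9D. The goal-based measure differs: participants "set up to three goals at baseline, with progress towards meeting these goals rated on a 10-point scale at the 6-month follow-up point", so no baseline progress rating is described.

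The article does use own-baseline adjustment in two other places. The sample size relies on it for the BAT ("Assuming a correlation of 0.5 between baseline and final BAT measure"), and the Economic evaluation says "The regression analysis will control for baseline differences in utility".

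**The concern.** In a randomised comparison of a 6-month score, the baseline value of the same score is usually the natural covariate. It tends to explain more outcome variance than another instrument's baseline, and it removes the effect of a chance difference between arms on that scale. Here the data are collected, but as written they are not used in the models for five secondary outcomes. EQ-5D-Y shows the inconsistency: its utility is baseline-adjusted in the economic regression, while the clinical comparison of the same instrument is written with baseline BAT.

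At stake is the precision of the secondary comparisons and their robustness to chance imbalance. The Introduction includes the wider impact of phobias on mental health and quality of life in the primary aim, and these secondary outcomes are what measure it.

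**Working it through.** **1. The plan's own figure.** The inputs, from the Sample size section, are a margin of 0.4 SD ("we set the non-inferiority margin to be half of this at 0.4"), 90% power, 2.5% one-sided significance and a baseline-final correlation of 0.5. With no true difference assumed,

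n per arm = 2(1 − r²)(1.960 + 1.282)² / 0.4².

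- r = 0.5: 2 × 0.75 × 10.51 / 0.16 = 98.5, so 99 (the article states 100).
- r = 0: 2 × 10.51 / 0.16 = 131.4, so 132.
- Design effect: 1 + 14 × 0.01 = 1.14, giving 114 per arm.
- Drop-out: 114 / 0.80 = 142.5, so 143 per arm and 286 in total.

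The figure reproduces, and it depends on adjusting the BAT for its own baseline.

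**2. Precision for a secondary outcome.** Let r_own be the correlation of the 6-month score with its own baseline, and r_BAT its correlation with baseline BAT. Neither is given for any secondary outcome. The 0.5 is borrowed from the BAT, and the other values are assumptions. The ratio of confidence interval widths, own baseline against baseline BAT, is

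√[(1 − r_own²) / (1 − r_BAT²)].

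| r_BAT | r_own = 0.3 | r_own = 0.5 | r_own = 0.7 |
|---|---|---|---|
| 0 | √(0.91/1.00) = 0.954 | √(0.75/1.00) = 0.866 | √(0.51/1.00) = 0.714 |
| 0.3 | √(0.91/0.91) = 1.000 | √(0.75/0.91) = 0.908 | √(0.51/0.91) = 0.749 |
| 0.4 | √(0.91/0.84) = 1.041 | √(0.75/0.84) = 0.945 | √(0.51/0.84) = 0.779 |
| 0.5 | √(0.91/0.75) = 1.102 | √(0.75/0.75) = 1.000 | √(0.51/0.75) = 0.825 |

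- r_own = 0.5: narrowing runs from 13% (r_BAT = 0) through 5.5% (0.4) to nil (0.5).
- r_own = 0.7: narrowing is 29% down to 17.5%.
- r_own = 0.3: narrowing is at most about 5% and nil at r_BAT = 0.3. Above that, baseline BAT is the better single covariate.

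The formula leaves out site, age group and baseline severity, which are in the model either way, so the results are illustrative.

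**3. In terms of power.** With 114 evaluable per arm, the effective number is 114 / 1.14 = 100 per arm and the SE is √[2(1 − r²)/100] in SD units. Power for a 0.4 SD difference is Φ(0.4/SE − 1.96). The 0.4 is only a yardstick here, since the article states no margin for any secondary outcome.

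- Baseline BAT, r_BAT = 0: SE 0.141, power 81%.
- Baseline BAT, r_BAT = 0.4: SE 0.130, power 87%.
- Own baseline, r_own = 0.5: SE 0.122, power 90%.
- Baseline BAT, r_BAT = 0.5: the same 90%, so no loss.

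**4. Chance imbalance.** Suppose the arms differ by 0.2 SD on a scale's own baseline, beyond what the stated covariates explain. About r_own × 0.2 then remains in the 6-month estimate: 0.06, 0.10 and 0.14 SD at r_own = 0.3, 0.5 and 0.7.

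**The case against.** **The covariate sentence may describe the BAT analysis only.** It speaks of one analysis, and the sentence after it gives the 0.4 rule, which belongs to the BAT. That reading is possible. But the sentence directly follows one naming all outcomes and is not restricted. If the restriction was intended, the text still needs the same clarification.

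**Outcome-specific covariates are usually left to the SAP.** True, and silence would be no finding. Here the article states a covariate set, and taken literally that set leaves out the own baselines.

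**Baseline BAT may be a good covariate for these scales.** A reader might infer that a count of approach steps predicts a questionnaire score poorly. The documents do not support this: the Behavioural avoidance task section reports a strong correlation with other anxiety and phobia measures. It gives no figure and does not say whether this is a baseline-to-6-month correlation, so it does not settle the size. It is the reason the range above runs up to r_BAT = 0.5, where the gain at r_own = 0.5 disappears.

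**Imbalance is already partly handled.** A reader might infer that it goes wholly uncorrected. It does not: baseline BAT removes whatever it shares with each scale, and severity, with "two phobia severity groups (mild to moderate vs severe"), is both a stratifier and a covariate and may help for ADIS in particular. A two-level phobia severity factor is still not a substitute for baseline RCADS, CAIS or CHU-9D scores.

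**Conclusion.** The point holds in a limited form. Taken as written, five of the six secondary outcomes (ADIS, CAIS, RCADS, EQ-5D-Y, CHU-9D) are not adjusted for a baseline score that the trial collects. Precision is probably lost, and chance imbalance is only partly corrected. At r_own = 0.5 the gain forgone is between about 13% of interval width and nothing, depending on an r_BAT the article does not give. At r_own = 0.7 it is larger, and at 0.3 little or none.

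Two wider conclusions might be inferred and should not be. First, the point does not reach every secondary outcome, because the goal-based measure has no baseline rating to adjust for. Second, it does not weaken the non-inferiority claim. That claim rests on the per-protocol and ITT analyses of the BAT, which is adjusted for its own baseline, and N=286 stands. Randomisation also keeps the secondary estimates unbiased on average. The issue is precision and conditional imbalance in secondary comparisons.

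**What to change.** Add one sentence to the Data analysis section stating that each secondary outcome with a baseline measurement (ADIS, CAIS, RCADS, EQ-5D-Y, CHU-9D) is adjusted for its own baseline value, site and the stratifying variables. Baseline BAT may be kept as an additional covariate. This guards against the case where it predicts a scale better than the scale's own baseline does, at the price of one degree of freedom. State that the goal-based outcome, rated only at 6 months, keeps the current covariate set. If the covariate sentence was meant for the BAT alone, say so and give the secondary covariates separately.

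The cost is a wording change: no new data, no change to the sample size and no change to the primary analysis. It should be settled before allocation is unblinded.

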#### The anxiety disorder interview schedule for children and parents

Anxiety disorder interview schedule (ADIS)^32^ is a well-established semistructured interview^3 32 33^ that obtains information from both the child and their parent/carer about the type of specific phobias experienced (eg, animal/insect, small spaces, blood/injection phobias, etc), the degree of associated fear (rated from 0=not at all to 8=very, very much), whether the phobia causes avoidance (rated as ‘yes’ or ‘no’) and interference with daily life (rated from 0=not at all to 8=very, very much).

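### The primary model leaves out phobia type although each stimulus has its own BAT ladder; adding one prespecified type factor could recover some precision

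*Protocol article*

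**What the plan says.** The Data analysis section specifies "mixed-effects linear regression with exchangeable correlation to allow for the clustering of outcomes within therapist" for BAT score at 6 months, and gives the covariates: "The analysis will be conducted controlling for baseline BAT score, site and stratifying variables (age group and baseline phobia severity"). The last two are the randomisation strata: "Randomisation is stratified according to two age groups (7–11 years old vs 12–16 years old") and "two phobia severity groups (mild to moderate vs severe").

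The Behavioural avoidance task section says that the BATs "are standardised for each stimulus", each with 10 predefined steps, and that the number of steps taken is what is analysed. The Participants section admits every type of phobia whose stimulus can be introduced or safely simulated. The ADIS, completed at baseline and 6 months, obtains information "about the type of specific phobias experienced (eg, animal/insect, small spaces, blood/injection phobias, etc"). Phobia type is therefore in hand before randomisation, but it is neither a stratifier nor a listed covariate.

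The same section makes per protocol the main analysis, defined by attendance: both the assessment and the exposure session for one-session treatment (OST), at least four sessions for CBT. Per-protocol and intention-to-treat (ITT) analyses must both succeed for non-inferiority to be declared.

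**The concern.** A step count means something different on each ladder. Step 10 for spiders is holding the spider for 20 s, and the article does not say that step 10 is equally hard for other stimuli. The model nevertheless pools raw step counts with one intercept for all types. If ladders differ in how many steps are attainable, whatever part of that difference baseline BAT does not absorb stays in the residual variance and widens the confidence interval that is compared with the margin.

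The per-protocol set adds a second reason. It is selected after randomisation by a different attendance rule in each arm, so randomisation no longer guarantees that the arms are balanced on phobia type there. Because both analyses must succeed, imprecision or imbalance in either one can leave the trial inconclusive.

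**Working it through.** **Inputs from the Sample size section.** Margin 0.4 SD; baseline–final correlation 0.5; one-sided 2.5%; 90% power; 15 patients per therapist with ICC 0.01; 20% drop-out.

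**Reproducing the plan.**
- Residual variance given baseline BAT: 1 − 0.5² = 0.75.
- Per arm before clustering: 2 × (1.960 + 1.282)² × 0.75 / 0.4² = 98.5, so 99 (stated 100).
- Design effect: 1 + 14 × 0.01 = 1.14; 100 × 1.14 = 114 per arm.
- Drop-out: 114 / 0.8 = 142.5, so 143 per arm and 286 in total, as stated.
- SE with 114 analysed per arm: √(2 × 0.75 × 1.14 / 114) = 0.1225.
- Power: Φ(0.4 / 0.1225 − 1.96) = 90.4%. (Using 143 × 0.8 = 114.4 per arm gives 90.5%.)

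The planned power is met with baseline BAT alone; nothing in it relies on phobia type.

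**Adding phobia type.** Let R² be the further share of residual variance that type explains. The documents give no value, so the range is assumed. The SE becomes 0.1225 × √(1 − R²). For the degrees of freedom I assume 4 dummy variables and about 8 parameters already in the model, which multiplies the residual variance by (228 − 8)/(228 − 12) = 1.0185. Equivalent extra children are 228/(1 − R²) − 228, before that cost.

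| Added R² | SE | Power before df cost | Power after df cost | Equivalent extra analysed children |
|---|---|---|---|---|
| 0% | 0.1225 | 90.4% | 89.9% | 0 |
| 2% | 0.1212 | 91.0% | 90.5% | about 5 |
| 5% | 0.1194 | 91.8% | 91.3% | 12 |
| 10% | 0.1162 | 93.1% | 92.7% | about 25 |

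Basing the df cost on the effective sample of 200 (228 / 1.14) makes it slightly larger: 90.4%, 91.2% and 92.6% in the last three rows. Overall the cost is about 0.4 to 0.6 points, and the break-even R² is about 2%.

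**How much does baseline BAT already absorb?** Suppose a share f of BAT variance lies between ladders and shifts baseline and final scores equally, with equal SDs and overall correlation 0.5. The pooled slope is then 0.5, so baseline BAT removes only half of the shift. Within ladders the residual variance is (1 − f) − (0.5 − f)²/(1 − f), to be compared with 0.75.

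| Assumed f | Within-ladder residual variance | Recoverable share of 0.75 | Power after df cost (factor 1.0185) |
|---|---|---|---|
| 5% | 0.7368 | 1.75% | 90.4% |
| 10% | 0.7222 | 3.7% | 91.0% |
| 20% | 0.6875 | 8.3% | 92.2% |
| 30% | 0.6429 | 14.3% | 93.8% |

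An added R² of 2% to 10% is therefore compatible with baseline BAT already being in the model, but it requires a between-ladder share well above 5%.

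**The case against.** The case for leaving the model alone is strong. Adjusting for the baseline outcome, site and the stratifiers in the form used at randomisation is standard and valid. Omitting a prognostic covariate from a linear model neither biases a randomised comparison nor inflates its type I error, and the confidence interval already allows for chance imbalance. Baseline BAT absorbs part of any ladder difference, the size of the gain is an assumption, and below the break-even point the factor costs more than it returns. This is also a condensed article; an analysis plan that is not shown may add covariates. All of this stands. It limits the point to an optional gain in efficiency. It does not remove it, because baseline BAT is only a partial substitute for type and the per-protocol set does not have the full protection of randomisation.

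A reader might go further and infer that other baseline data should also enter the model. The documents do not support that:

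- **Continuous age.** For ages spread evenly over 7–16, the two-group split keeps about 76% of the linear age signal. Even if age explained 10% of residual variance, using years would raise power only from 90.5% to 91.2%.
- **A finer severity term.** The ADIS section describes fear and interference ratings from both child and parent and defines no single severity score. Baseline BAT already carries a graded 0–10 measure of avoidance.
- **Treatment preference.** "Children and parents are also asked if they have a treatment preference at baseline", but nothing in the article links preference to attendance. Adjusting for it only in the per-protocol model would give different covariates to two analyses that must agree.

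**Conclusion.** The point holds as a modest improvement to the analysis. The listed covariates omit phobia type even though the outcome ladder depends on it and the data are collected at baseline. Over an assumed added R² of 2% to 10%, the net change in power runs from nothing to a little over 2 points. This rests on 114 analysed per arm, the protocol's correlation of 0.5 and design effect of 1.14, a true difference of zero, and about 4 dummy variables for type.

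A reader might infer that the trial is underpowered, or that its primary comparison is biased, because type is missing. Neither follows: the stated sample size reproduces without type, and the randomised comparison is valid as written. For the per-protocol set the documents show only that balance on type is not guaranteed, not that imbalance will occur.

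**What to change.** Before unblinding, add one prespecified phobia-type factor to the covariate list under Data analysis. Use broad ADIS categories that correspond to the BAT ladder the child is tested on, and fix in advance the rule for merging small categories. Put the same factor in both the per-protocol and ITT models, so that the two required analyses have identical covariates. Leave age group and severity group as randomised, and do not add treatment preference.

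The cost is a sentence of protocol or analysis-plan wording and about 4 degrees of freedom out of about 228 analysed children. No new data are needed. The downside is a loss of about half a point of power if ladders turn out not to differ.
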